# A cluster randomized controlled trial comparing the effectiveness of two school-based interventions for autistic youth with anxiety

**DOI:** 10.1186/s12888-023-05441-0

**Published:** 2024-01-02

**Keywords:** Autism, Anxiety, Schools, Cognitive behavioral therapy (CBT), Implementation, Patient-centered outcomes

## Abstract

**Background:**

Recent systematic reviews have indicated that cognitive behavioral therapy (CBT) is effective in reducing anxiety symptoms for autistic and non-autistic children. However, the vast majority of CBT research for autistic youth has been implemented within university settings and primarily by mental health providers. Schools hold great promise to equitably manage the mental health symptoms of autistic youth. Although preliminary research evaluating CBT within schools has been promising, CBT has not yet been compared to another readily available school mental health program. The goal of this protocol paper is to describe a multi-site study comparing two school-based interventions, Facing Your Fears-School Based (FYF-SB) and Zones of Regulation (ZOR) via a cluster randomized controlled type 1 hybrid effectiveness-implementation trial to determine which of the two interventions will best support autistic youth with anxiety in schools.

**Methods:**

Up to 100 elementary and middle schools will be randomized into FYF-SB or ZOR. Once schools are randomized, a minimum of two interdisciplinary school providers at each school will be trained to deliver either FYF-SB or ZOR over the course of 12 weeks to groups of 2–5 autistic students ages 8–14 years*.* Over the course of two years, a total of 200 autistic students will receive either ZOR or FYF-SB. The primary outcome of this trial is child anxiety, as rated by masked evaluators and via caregiver- and student-report, which will be measured at baseline, post-treatment, and 6-month follow-up. Semi-structured interviews will also be conducted with a purposive sample of students, caregivers, and school providers to understand the acceptability, appropriateness, and feasibility of either ZOR or FYF-SB. Stakeholder engagement is a central component of this project via two stakeholder advisory boards that will directly inform and oversee the project.

**Discussion:**

Results of this study will provide evidence about the relative impact of two school-based mental health interventions on outcomes reported as meaningful by caregivers and school providers. The additional focus on evaluating factors that support the implementation of FYF-SB and ZOR will allow future studies to test targeted implementation strategies that support mental health programming uptake and implementation within public schools.

**Trial registration:**

This trial is registered with clinicaltrials.gov (NCT05863520).

**Supplementary Information:**

The online version contains supplementary material available at 10.1186/s12888-023-05441-0.

## Background

As many as 40% of autistic youth develop co-occurring clinical anxiety that can significantly limit their participation and quality of life across multiple contexts [1]. For example, in schools, anxiety can limit students’ attendance, school performance, peer relationships, and extracurricular participation [2–5]. Unfortunately, autistic youth with anxiety have experienced longstanding challenges accessing mental health care in community settings [6, 7]. Difficulties accessing mental health services are even more pronounced for youth from minoritized backgrounds, whose mental health symptoms may go undetected or misinterpreted, thus, limiting their access to care or leading to punishment-based interventions [4]. Youth from minoritized communities were also disproportionately affected by the COVID-19 pandemic, as service access was reduced due to long wait lists and a shortage qualified providers [8, 9]. Without equitable access to evidence-based mental health care, underserved autistic individuals may experience more impairing anxiety over time, further impacting their quality of life [10].

Recent systematic reviews have indicated that cognitive behavioral therapy (CBT) is an evidence-based practice (EBP) that is effective in reducing anxiety symptoms for children with and without autism [11, 12]. However, the vast majority of CBT research for autistic youth has been implemented within university settings and primarily by mental health providers (e.g., psychologists) [12, 13]. Schools hold great promise to equitably manage the mental health symptoms of autistic youth. Approximately 65% of autistic youth receive mental health services within schools [14], and youth with minoritized identities often only access mental health services within school settings [15]. Yet most autism research conducted within schools has focused on the implementation of social communication interventions for young autistic children [16, 17], rather than interventions focused on improving anxiety and other mental health outcomes.

CBT has been successfully implemented in schools for non-autistic youth with anxiety symptoms [18, 19], and a handful of studies have adapted CBT for autistic youth with anxiety for school-based delivery, with encouraging results [20, 21]; however, the long-term viability of such programs is limited, since these studies relied heavily on research personnel to deliver or co-deliver these interventions rather than school-based personnel. Further, in the absence of formal training in CBT, general and special education teachers are less likely to use CBT core components such as encouraging autistic students to face their fears students [22]. To address the significant mental health needs of autistic students, there is a critical need to build the capacity for school-based providers to deliver EBPs without continued support from clinical providers. Importantly, training non-autism experts offers the possibility to dramatically expand capacity to serve autistic youth [16].

Our team has attempted to address this gap through the development of the Facing Your Fears-School Based Program (FYF-SB), an evidence-based group CBT intervention that can be delivered by interdisciplinary school providers (ISPs) to anxious autistic youth [23–25]. FYF-SB was derived from FYF, an empirically supported, clinic-based, outpatient group CBT program for autistic youth ages 8–14 years. FYF-SB was iteratively adapted through extensive caregiver, school provider, and school administrator input that underscored the lack of available and appropriate school-based interventions for anxious autistic youth and necessary adaptations to FYF for school-based delivery [26]. FYF-SB was then piloted by 25 ISPs (e.g., school psychologists, special educators, speech language pathologists) and delivered to 29 students with autism. Results indicated that significant reductions in anxiety occurred following program participation [27]. Following the feasibility trial, 81 students with autism or suspected autism and anxiety were randomized to either FYF-SB or usual care. ISP fidelity to FYF-SB was strong and significant reductions in anxiety were apparent for students receiving FYF-SB relative to students in usual care according to parent- and student-report [28].

Results from these initial trials are promising, yet FYF-SB has not yet been compared to another readily available school mental health program. Indeed, sweeping reviews of CBT effectiveness also indicate that although CBT approaches have consistently demonstrated superiority to wait list or no treatment, there is no clear evidence that CBT is more effective than other interventions for anxiety. The current trial aims to address this gap by comparing FYF-SB to the Zones of Regulation (ZOR) [29], a manualized school-based intervention that does not have an established evidence base [30], yet is in wide-spread use with over 300,000 books sold and thousands of educators having delivered the program [31]. ZOR is also rooted in CBT principles and uses a metacognitive framework to increase emotion regulation skills by increasing awareness of feelings and building regulation, prosocial skills, and overall wellness. Emotion dysregulation is common in autistic youth, is a correlate of anxiety, and is a transdiagnostic factor that underlies various psychiatric conditions, including anxiety, depression, and other mood disturbance [32]. Given its underlying role in mental health conditions, emotion regulation is a critical target of anxiety-based interventions.

Comparing the effectiveness of FYF-SB and ZOR is also important given that ZOR and FYF-SB have related but distinct treatment approaches. That is, although both interventions are rooted in CBT principles, ZOR primarily uses psychoeducation and direct teaching of coping strategies to improve self-regulation, while FYF-SB pairs psychoeducation with graded exposure in which students practice facing their fears a little bit at a time to reduce anxiety symptoms. Although graded exposure plays a critical role in anxiety outcomes and is considered a core component of CBT [33, 34], previous research has demonstrated that graded exposure is often a novel treatment strategy for school-based providers that may be logistically complicated to implement within schools [35]. Thus, in addition to their distinct intervention targets, comparing ZOR and FYF-SB may provide insight into the feasibility of each intervention’s core components when implemented within school settings.

The goal of this protocol paper is to describe a multi-site study comparing two school-based interventions, FYF-SB and ZOR via a cluster randomized controlled type 1 hybrid effectiveness-implementation trial [36] to determine which of the two interventions will best support autistic youth with anxiety in schools. Elementary and middle schools will be randomized to deliver either FYF-SB or ZOR to autistic students with interfering anxiety in small group format*.* Specific aims are as follows: 1) Compare the effectiveness of FYF-SB and ZOR on: (a) symptoms of anxiety (primary) and emotion dysregulation (co-primary) as rated by caregivers, students, teachers, and masked research staff; and (b) functional outcomes of priority to stakeholders, including school attendance, disciplinary action, and academic participation; 2) Compare the acceptability, appropriateness, and feasibility of FYF-SB and ZOR and a range of factors that contribute to the successful implementation of these two programs within schools; and 3) Examine autism severity and anxiety symptom severity as moderators of treatment response.

Results of this study will expand the intervention and implementation literature for autistic youth with co-occurring mental health conditions by providing evidence about the relative impact of two school-based mental health interventions on outcomes reported as meaningful by caregivers and school providers. The additional focus on evaluating factors that support the implementation of FYF-SB and ZOR will allow future studies to test targeted implementation strategies that support mental health programming uptake and implementation within public schools in order to meet the needs of autistic students and their families.

## Methods

### Study setting

The current trial takes place within public school districts and charter schools across two states representing racial, ethnic, economic, and geographic diversity (i.e., Colorado and North Carolina). Participating districts include large, medium, and small districts serving both urban and rural communities. Recruitment will be prioritized to occur within elementary and middle schools with high rates of free and reduced lunch as well as racially and ethnically diverse student populations.

### Stakeholder involvement

Stakeholder engagement is a central component of this project via two stakeholder advisory boards (SABs) that will directly inform and oversee the project. The first SAB is composed of parents of autistic youth, school providers and administrators from participating districts, as well as autistic adults with experience participating in CBT. The second SAB is composed of a minimum of 6 high school autistic students (High School-Stakeholder Advisory Board; HS-SAB) from Colorado and North Carolina. They will be asked to share their lived experience with autism and anxiety in schools and what kinds of support would have been most helpful to them as younger students. The two SABs will meet a minimum of twice yearly and inform all phases of the project, including advise on recruitment strategies, trouble-shoot challenges with conducting the research, review quantitative and qualitative data, and provide recommendations for communicating research findings to study participants. Finally, an autistic adult is a co-investigator on the research team, in a shared decision-making role. She will attend regular research team meetings and co-facilitate both SABs.

### Procedures

School administrators from each partnering school district will first identify elementary and middle schools in their districts that serve a high proportion of historically underserved youth (e.g., racial/ethnic minority youth; high rates of free and reduced lunch). If they are unable to recruit enough participants from those schools, then district leaders will turn to other schools within their district for recruitment. Two-hundred autistic students from up to one hundred (100) schools across Colorado and North Carolina will be randomized to either ZOR or FYF-SB over the course of the project, with up to 50 schools randomized during one academic year and another 50 schools randomized over a second academic year. Once schools are randomized to condition, a minimum of two ISPs at each school will be consented and participate*.* All ISPs will receive training on how to recognize anxiety and emotion dysregulation in autistic students followed by training in either FYF-SB or ZOR.

After training, ISPs will nominate students in their school that they suspect may meet the study inclusion criteria to form groups of 2–5 students with autism and co-occurring anxiety. Once the screening and qualification processes have been completed, and informed consent/assent has been obtained by trained research staff, pre-intervention measures will be completed. Caregiver- and teacher-report measures may be completed electronically via REDCap while student self-report measures will be completed in person by a member of the research team. If students meet inclusion criteria, they will be given the option to assent into the study. Assent will be obtained at their school and by trained research staff. If they assent, participating students will receive either ZOR or FYF-SB depending on which condition their school was randomized to. FYF-SB and ZOR will be delivered over 12 weeks for a duration of approximately 40 min for each lesson. Post-intervention measurements will be completed within 4 weeks of program completion. Semi-structured exit interviews will be conducted with a purposive sample of students, caregivers, and ISPs to obtain information regarding acceptability, appropriateness, and feasibility of either ZOR or FYF-SB, along with any potential harms. Selected outcome measures will be completed at 6 months follow-up.

### Interventions

*Facing Your Fears-School Based* (*FYF-SB)* is derived from FYF, an evidence-based outpatient clinic program for autistic youth (and their caregivers) between the ages of 8–14 years [37]. The original FYF program is a 14 week, 90-min, group CBT intervention focused on the management of clinically significant anxiety symptoms. Seven treatment studies have been conducted on FYF, including a randomized trial, a multi-site randomized trial, and several pilot studies adapting FYF for different populations [23, 24, 27]. FYF-SB was adapted for school-based delivery based on stakeholder input and is a group CBT program [26]. Consistent with the original program, FYF-SB consists of psychoeducation (e.g., identification of anxious symptoms, somatic management strategies, use of positive self-statements) and graded exposure practice (facing fears a little at a time). Worksheets include many visuals, paired with clear written directions, and multiple-choice lists. Brief “hands-on” activities and video modeling enhance accessibility of CBT content for different learners. Culturally appropriate representations of students from diverse racial/ethnic backgrounds are incorporated throughout the materials, and this program has been delivered to students from historically underserved backgrounds. Results from a pilot feasibility study and randomized trial have demonstrated effectiveness of FYF-SB compared to usual school care [27].

*Zones of Regulation (ZOR)* uses a metacognitive framework to increase awareness of feelings, as well as various tools and strategies to improve regulation and build prosocial skills and overall wellness. “Mindfulness, sensory integration, movement, thinking strategies, wellness and healthy connections” are examples of some of the tools and strategies included in ZOR. ZOR is an inclusive strategy for neurodiverse learners who have specific social/emotional and/or behavioral needs [29]. ZOR incorporates Social Thinking concepts to support students to identify feelings, identify level of alertness and understand how their behaviors can impact outcome. ZOR is rooted in CBT principles and supports students to self-monitor their own behaviors and eventually engage in management strategies independently. As mentioned, ZOR is clearly in widespread use and has been delivered by thousands of educators. In this study, ZOR will be delivered in small groups and with similar duration and frequency as FYF-SB*.* See Table 1 for a depiction of the core components of FYF-SB and ZOR.

**Table 1 Tab1:** Core activities of FYF-SB and ZOR

	**Facing Your Fears**	**Zones of Regulation**
**Psychoeducation**		
Identification and understanding emotions	X	X
**Introduction and practice of coping skills**		
Coping skills specific to anxiety	X	
Teaching cognitive reappraisal	X	
Creation and externalization of "worry bully"	X	
Understanding impact of emotions on others		X
Use of sensory regulation strategies		X
**Exposure**		
Practice facing fears a little at a time	X	
**Generalization**		
Handouts shared with caregivers	X	X
At least one point of contact with caregivers	X	

### Randomization

Schools within each state will be randomized with 1:1 ratio into FYF-SB or ZOR comparators. To minimize the imbalance in participant age, randomization will be stratified by school type (elementary versus middle school). The unit of intervention and randomization will be at the school level in order to feasibly train ISPs for one type of intervention and to prevent contamination of comparators within a school across students.

### Training workshops

Both the ZOR and FYF-SB training workshops will be approximately 12 h in duration. The trainings will be scheduled in collaboration with the participating school districts. Each training will include an initial segment (3-h overview) on how to identify anxiety and emotion dysregulation in students with autism so that ISPs will be best prepared to nominate students for participation in the study. Additional content of the workshops will vary by intervention approach, but will include a conceptual overview of the program, as well as session by session review. Both trainings will include a combination of didactic presentations and discussion. Some trainings will be delivered virtually while others will be delivered in person (per school district choice). Checklists for fidelity to the training will be used to ensure that all trainings are conducted in the same manner.

### Consultation

The ISPs teams will participate in bi-monthly consultation sessions (20–30 min) via phone or video call with a member of the research team, for the duration of the time they deliver the intervention for a maximum of 6 consultation calls (i.e., 3 h) per school team. The consultation format for each call will include opportunities for reflection on group facilitation as well as the following components: (a) informal question and-answer period; (b) provision of feedback regarding strengths of facilitation, missing elements, and suggestions for delivery of session content; and (c) plan for the upcoming sessions. The ZOR consultation will be provided by research team members trained to reliably provide consultation in ZOR. Similarly, the FYF-SB consultation will be provided by trained research personnel.

### Participants

#### Interdisciplinary school providers (ISPs)

Recruitment will include up to 200 ISPs who (1) are degreed professionals in one of the following: education (special or general education), school psychology, counseling, social work, speech/language pathology, occupational or physical therapy; and (2) work with autistic students with anxiety. ISPs must also be able to complete study requirements including attending the training workshops, delivering at least 80% of the program they were randomized to, and participating in 80% of bi-monthly consultation sessions with the research team. At least two ISPs per school team will facilitate the FYF-SB or ZOR groups. It is recommended that the ISP teams have access to ongoing consultation with a school mental health provider. Paraprofessionals can be enrolled as ISPs, provided that their role is to assist other ISPs, rather than lead the groups themselves.

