Implementation climate. ISPs will rate their school’s evidence-based practice (EBP) implementation climate using the Implementation Climate Scale (ICS) [51]. The ICS includes 18 items rated on a Likert scale from 0 (not at all) to 4 (very great extent). Items are averaged to produce a total score. Item content covers six domains, including focus on EBPs, educational support for EBPs, recognition for EBPs, rewards for EBPs, selection for EBPs, and selection for openness. The scale is psychometrically validated and has been used in other studies examining the implementation of autism EBPs within schools [51, 52].

Intervention fidelity*.* Two separate but similar treatment fidelity checklists will be used to document treatment adherence as well as provider competence in delivering core components of FYF-SB or ZOR. The measures will assess the ISPs’ adherence to their assigned intervention by assessing the presence/absence of core components as well as the quality of intervention delivery. In ZOR*,* the checklist will measure ISPs’ adherence to the four key elements of preparation, provision of structure, quality of facilitation, and adult evaluation of student learning. In FYF-SB, the checklist will measure ISP’s adherence to core activities included within each session. It will also include an overall competence rating in which ISP’s Both FYF-SB and ZOR fidelity will be coded by trained research team members with reliability calculated on 15–20% of scored sessions.

Implementation survey. At the conclusion of delivering FYF-SB or ZOR, ISPs will rate the feasibility, acceptability, and appropriateness of their respective intervention, including the likelihood that providers will continue to implement the intervention once the study has ended. Providers will rate each of 36-items using a 5-point Likert scale. This survey was adapted from several different sources [53] and is designed to examine intervention feasibility, acceptability, and appropriateness for the school setting. An adapted version of this survey has been used in other studies examining the feasibility of interventions for autistic youth, including in our previous school trials [27, 28].

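### Aim 2 is open to post-randomization selection: ISPs enter with the arm known, must be able to deliver 80% of it, and rate feasibility only when delivery concludes

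*Protocol article*

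**What the plan says.** Four statements in the Protocol article bear on this point.

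- **Order of events.** Under Randomization: "The unit of intervention and randomization will be at the school level". Under Procedures: "Once schools are randomized to condition, a minimum of two ISPs at each school will be consented and participate". ISPs therefore join when their school's programme is already fixed.
- **Requirement on ISPs.** Under Interdisciplinary school providers (ISPs), the requirements that ISPs must be able to meet include workshop attendance and "delivering at least 80% of the program they were randomized to, and participating in 80% of bi-monthly consultation sessions". The delivery threshold refers to the assigned programme.
- **Timing of the rating.** Under Implementation measures, for the implementation survey: "At the conclusion of delivering FYF-SB or ZOR, ISPs will rate the feasibility, acceptability, and appropriateness of their respective intervention". No earlier ISP feasibility rating is described.
- **Use of the rating.** Aim 2 (end of Background; Analytic plan) compares the two programmes on feasibility, acceptability and appropriateness. The quantitative data are modelled as an outcome without repeated measures. Intention to treat is stated for the primary analysis.

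The Background also says of the component that Table 1 lists for FYF-SB alone: "graded exposure is often a novel treatment strategy for school-based providers that may be logistically complicated to implement within schools".

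**The concern.** Whether a provider can deliver the assigned programme is part of what Aim 2 sets out to measure. The same ability is also a condition of taking part, and it is judged once the arm is known. An ISP who thinks the assigned programme cannot be delivered in that school may decline or not qualify. An ISP who starts and gives up has no conclusion of delivery at which to be surveyed. Either way, the least favourable views are the ones most likely to be missing.

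If this happens more often in one arm, the ISPs who remain are no longer comparable by randomization, and the programme that is harder to deliver looks better than it should. The Discussion says that results on strengths and weaknesses are meant to help school leaders choose a programme. An understated feasibility difference would bear directly on that use. The primary anxiety outcomes are not at issue here.

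**Working it through.** The document gives no figure for this point, so the check is mainly of the text, followed by a calculation of direction.

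**1. What the thresholds mean.** Procedures: "FYF-SB and ZOR will be delivered over 12 weeks for a duration of approximately 40 min for each lesson". If there is one lesson a week (my assumption), 0.80 × 12 = 9.6, so at least 10 of 12 lessons. Consultation: "for a maximum of 6 consultation calls (i.e., 3 h) per school team". Then 0.80 × 6 = 4.8, so at least 5 of 6 calls. The margin is narrow: two missed lessons, or one missed call.

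**2. Where ISPs can be lost, in order.**
- After allocation, before consent: an ISP may decline or be judged unable to meet the requirement. No rating exists.
- After consent, before delivery ends: an ISP may stop. Read literally, the survey trigger is never reached.
- At the end of delivery: the remaining ISPs are surveyed once.

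**3. Whether another feature fills the gap.**
- *Mixed models under missing at random.* With a single rating per ISP, a missing survey leaves no earlier rating from that ISP for the model to use. Non-response because delivery proved infeasible would also not be missing at random.
- *Intention to treat.* It is stated for the primary analysis, and it cannot restore ISPs who were never consented.
- *Fidelity coding.* It scores adherence and quality in delivered sessions, with a separate checklist for each programme. It is not a common measure of how much was delivered.
- *Exit interviews.* They are qualitative, cover a subset and also come at the end.

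**4. Direction of the bias.** Suppose true feasibility has SD 1 in each arm and means that differ by d. Suppose an ISP is surveyed only if a second variable, correlated ρ with feasibility, exceeds a cut-off c common to both arms. Let p_A be the share surveyed in the easier arm and p_B the share in the harder arm. Then

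observed difference = d − ρ(λ_B − λ_A), with λ_A = φ(c)/p_A and λ_B = φ(c + ρd)/p_B.

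Worked case: d = 0.5, ρ = 1, p_A = 0.95, so c = −1.645. λ_A = 0.103/0.95 = 0.109. For the harder arm c + ρd = −1.145, p_B = 0.874 and λ_B = 0.207/0.874 = 0.237. Observed difference = 0.5 − (0.237 − 0.109) = 0.37.

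Simulation of the same model with d = 0.5 gives:

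| p_A | ρ = 0 | ρ = 0.5 (p_B) | ρ = 1 (p_B) |
|---|---|---|---|
| 0.95 | 0.50 | 0.47 (0.92) | 0.37 (0.87) |
| 0.85 | 0.50 | 0.45 (0.78) | 0.28 (0.70) |
| 0.70 | 0.50 | 0.43 (0.61) | 0.22 (0.51) |

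If selection is unrelated to feasibility, nothing is lost. At ρ = 0.5 the survey keeps 86% to 95% of the true difference; at ρ = 1 it keeps 43% to 74%. Every input (d, ρ and p_A) is assumed, and the document supplies none of them.

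**The case against.** The strongest reply is that the 80% wording is a forward-looking commitment. Consent precedes training and delivery, so nobody can be screened at entry on delivery that has not yet happened. No section withdraws, replaces or leaves unsurveyed an ISP who falls short. This stands. A reader might infer that Aim 2 compares the programmes mainly among providers for whom they proved feasible; the document does not support that.

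Second, the survey wording may fix only the timing and not who receives it. The Measures section ties measures to study time points, the schedule in Table 2 is not legible in the text at hand, and follow-up of ISPs who stop may be set out in the full protocol. This stands in part. It is why the point is limited to what the stated trigger does if followed literally, and why the absence of a named Aim 2 analysis set is not itself criticised.

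Third, the Background says only that exposure is often new and may be complicated, and it reports strong ISP fidelity to FYF-SB in the earlier randomized trial. It would go too far to say that the document expects more FYF-SB providers to drop out. It does give a reason why ability to deliver could differ by arm, and that is enough for a risk.

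Fourth, a type 1 hybrid trial with anxiety as its primary outcome has good reason to protect delivery. This stands, and it argues against removing the 80% commitment. It does not argue against collecting ratings from ISPs who miss it.

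Fifth, other Aim 2 evidence exists. That is correct, but as shown in the working it does not supply a between-arm comparison that includes ISPs who stop or schools that deliver little.

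**Conclusion.** The concern holds as a risk built into the stated design. The entry requirement depends on the assigned arm and applies after randomization, and the only structured ISP feasibility rating described is triggered by finishing delivery. Two gaps follow from the text if it is applied as written: ISPs who stop early contribute no rating, and the amount of programme delivered, itself a direct sign of feasibility, is not compared between arms.

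The likely bias is towards no difference. That rests on two assumptions: entry or completion is positively related to feasibility, and much the same bar applies in both arms. The size cannot be derived from the document; the range in the working runs from no attenuation to loss of more than half of a true difference. A reader might also infer that the trial will report the two programmes as equally feasible. That does not follow, because those who finish the harder programme may still rate it lower, and part of the difference would then show. This is an inexpensive improvement to a secondary aim.

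**What to change.** - **Interdisciplinary school providers (ISPs).** Keep the 80% figure as a delivery expectation. Add that it does not determine who is surveyed or who is analysed in Aim 2.
- **Implementation survey.** Give it to every consented ISP at the planned end of the 12 weeks, or at the time of stopping for those who stop earlier.
- **Aim 2 outcomes.** Add the share of sessions delivered per school, together with a yes/no for reaching 80%. Compare both by assigned arm with every randomized school in the denominator, so that a school that delivers nothing counts as zero.
- **Reporting.** Give by arm the number of schools and ISPs that decline after allocation. Their ratings cannot be recovered, but the counts show whether selection differed.

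The cost is small: wording changes, an existing survey sent to a few more people, and a session count per school. The drawbacks are some non-response among ISPs who stop and a little more tracking. Delivery in the effectiveness comparison is unaffected because the commitment stays.
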